**8. DEVELOPMENT OF TRIAL AND ASSESSMENT OF RESPONSE**

**8.1. PRINCIPAL AND SECONDARY ASSESSMENT VARIABLES**

**Efficacy criteria**

- Primary efficacy evaluation variable: Reappearance of clinical digestive signs (24 weeks)
- In addition, secondary efficacy variables will be evaluated:
  - Clinical signs at 4 weeks
  - Clinical signs at 12 weeks
  - Flow cytometry to measure percentage of lymphocytes CD3+ gamma-delta+ and CD3- in intestinal mucus membrane
  - Assessment of IgA tissue anti-transglutaminase antibodies in the intestinal mucus membrane
  - IgA tissue anti-transglutaminase antibodies in serum and anti-endomysium antibodies
  - Quality of life according to the GIQLI questionnaire.
  - Histological changes on biopsy in the distal duodenum

**Safety criteria**

The gluten-free diet in itself is entirely free of side effects. Nevertheless, a registry of typical side effects will be maintained throughout the study.

**8.2. DEVELOPMENT OF TRIAL, NUMBER OF VISITS, COMPLEMENTARY EXPLORATIONS**

The subjects will be selected according to the inclusion and exclusion criteria established in this protocol. In the event of a patient fulfilling the inclusion criteria and none of the exclusion criteria, he or she will be informed of the existence of the study, of its characteristics, and of the advantages and disadvantages in participating in it. Patients will be given an information sheet and their consent to participate in the study will be requested.

Those patients agreeing to take part in the study will receive a numerical code with which they will randomly receive one or the other of the medical treatment types.

After the start-up, the subject will be seen at 1, 3, and 6 months, as stipulated, and more frequently if necessary.

In the pre-inclusion visits, comprehensive bloodwork, coeliac serology, coeliac genetic study (HLA-DQ2/HLA-DQ8, if not already done), and distal duodenal biopsy, for pathological anatomy and flow cytometry, will be carried out.

**8.3. DESCRIPTION OF METHODS USED TO ASSESS RESPONSE**

Clinical response will be measured with analogue visual scales ranging from 0 to 100, administered at baseline and at each visit up to 6 months, for symptoms of abdominal pain, abdominal swelling, diarrhea, and flatulence (total score 0 to 400 points) (Appendix 6).

Patient quality of life will be evaluated in the first visit and the last (at 6 months, or at early withdrawal) using the GIQLI questionnaire (Gastrointestinal Quality of Life Index), which has been shown to yield valid, reliable scores for the detection of significant clinical changes in the lives of patients regarding their health (Eypasch E et al. Gastrointestinal Quality of Life Index: development, validation and application of a new instrument. Br J Surg 1995; 82:216-22; Quintana JM et al. Translation and validation of the Gastrointestinal Quality of Life Index (GIQLI). Rev Esp Enferm Dig 2001; 93:693-706) (See Appendix 3).

At the first visit and the last (or at early withdrawal from the study) a distal duodenal biopsy will be drawn for histological study, and evaluation of tTG deposits and lymphocytic sub-populations (using flow cytometry) will be made.

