# 1. SUMMARY OF THE STUDY

| **Title** | Lymphocytic enteritis with negative coeliac serology and clinical and histological response to a gluten-free diet: double-blind randomized clinical trial with rechallenge of gluten vs. placebo. | |
| --- | --- | --- |
| **Study code** | EL-DSG/07/2011 | |
| **Objectives** | To demonstrate hypersensitivity to gluten in patients with lymphocytic enteritis, and clinical response and histology of a gluten-free diet despite the presence of IgA negative tissue anti-transglutaminase antibodies. | |
| **Treatment** | Sachets with gluten (10 g) or placebo (maltodextrin: 10 g): 1 sachet every 12 hours. | |
| **Study design** | Prospective, randomized, double-blind, placebo-controlled, with parallel groups of gluten rechallenge vs. placebo, for 24 weeks, in patients following a gluten-free diet.   - Group A: Powdered gluten (10 g every 12 hours) - Group B: Placebo (10 g every 12 hours)   Determination of digestive clinical state, adherence to diet, coeliac serology, histology, flow cytometry, and tissue anti-transglutaminase antibodies in intestinal mucus membrane, at baseline and after gluten rechallenge or placebo (whether clinical digestive symptoms reappear at 4 or 12 weeks, or at the conclusion of the study at 24 weeks). | |
| **Study population** | Inclusion criteria:  1. Signed informed consent  2. Age 18 or older  3. Confirmed histological diagnosis of lymphocytic enteropathy (LE)  5. Coeliac-positive genetic study (HLA-DQ2 and/or HLA-DQ8)  6. Negative coeliac serology  7. Complete clinical and histological response to gluten-free diet  8. Initial clinical signs with or without extra-intestinal manifestations | |
|  | Exclusion criteria:  1. Inability to adhere to the scheduled visits or other protocol requirements, in the judgement of the investigator  2. Participation in a clinical trial in the previous 30 days, simultaneous participation in a trial, or prior participation in the present study  3. History of gluten-sensitive enteropathy with villous atrophy or positive serology  4. Lymphocytic enteropathy or initial response to gluten-free diet but following a normal diet at the time of selection | |
| **Sample size** | 20 patients | |
| **Length of treatment** | 24 weeks | |
| **Primary efficacy variables** | Reappearance of clinical digestive signs and histological recurrence | |

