**13. STATISTICAL ANALYSIS**

The calculation for the sample size is based on the main variable of efficacy—that is, the rate of recidivism at 6 months. On the basis of results of previous studies it was determined that the rate of recidivism with the reintroduction of gluten would be 80%, and with placebo 20%. Assuming a 10% patient drop-out rate, an alpha value of 5%, and statistical power (beta) of 80%, for a bilateral test it was calculated that 10 patients would be needed for each patient group (bearing in mind that analyzing the results would require a Chi-square test with Yates correction). The total number, then, is 20 patients.

Excluded from this analysis are those subjects presenting significant departures from the protocol.

All of the evaluations of the primary and secondary variables, both of efficacy and of safety, are understood in the exploratory sense (alpha=0.05, bilateral).

The Chi-square test with Yates correction will be used for independent groups and the Fisher exact test for qualitative variables. For intergroup comparison of the quantitative variables, the Student-t test will be used for parametric variables, and the Mann-Whitney U-test for non-parametric variables.

The finding of values for differences of p less than 0.05 will be considered significant. The rates for clinical remission between treatment groups will be expressed proportionally with the corresponding bilateral interval of confidence of 95%, as an estimation of therapeutic effect.

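### The primary event, reappearance of digestive symptoms, has no rule tying it to the 0–400 symptom total, yet it is judged during the trial and times the final biopsy

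*Protocol*

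**What the plan says.** Four places in the protocol bear on the primary event.

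- **Section 8.1** names it: "Primary efficacy evaluation variable: Reappearance of clinical digestive signs (24 weeks". Histological change is listed there as secondary.
- **Section 1 (Summary)** gives a different primary variable: "Reappearance of clinical digestive signs and histological recurrence". Its design row schedules the post-challenge determinations (symptoms, serology, histology, flow cytometry, tissue antibodies) by "whether clinical digestive symptoms reappear at 4 or 12 weeks", or otherwise at week 24.
- **Section 8.3** (form in Appendix 6) measures clinical response at baseline and every visit by scales for pain, swelling, diarrhoea and flatulence, with "total score 0 to 400 points".
- **Section 13** bases the sample size on "the rate of recidivism at 6 months", assuming that "the rate of recidivism with the reintroduction of gluten would be 80%, and with placebo 20" per cent, with "an alpha value of 5" per cent "for a bilateral test". It later speaks of clinical remission rates.

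No section says what total, what rise from baseline, or how many returning symptoms make a reappearance. The neighbouring terms are equally open: complete response at entry (6.1) and progression relative to baseline as a withdrawal reason (8.4) carry no number. Section 6.1 does give a numeric definition of lymphocytic enteropathy, so the protocol sets numeric rules elsewhere.

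**The concern.** A protocol can often leave the coding of an endpoint to its analysis plan. Here it cannot, because the event acts during the trial. At weeks 4 and 12 someone must decide whether symptoms have reappeared, and that decision fixes when the biopsy, cytometry and other closing assessments are taken. Two investigators looking at the same total may decide differently, and an analysis plan written later cannot restore the visits and biopsies that a different decision would have produced.

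Two things are at stake:

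- **Inconsistent classification under blinding.** It affects both arms alike and pulls the two relapse rates together. In a trial of 20 patients this is costly.
- **A cut set late.** If the event were re-derived from the scores after the code was broken, the cut could be chosen to suit the result.

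Three different terms (reappearance, recidivism, remission) and two different primary variables make it harder still to know which event is being counted.

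**Working it through.** **Inputs from the protocol.** Rates of 80% and 20%, two-sided alpha 0.05, power 80%, 10% drop-out, chi-square with Yates correction, 10 per group (section 13); 1:1 allocation (5.1).

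**Step 1: the plan's own figure.** With z = 1.960 and 0.842, a mean rate of 0.5 and a difference of 0.6:

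n = [1.960·√(2·0.5·0.5) + 0.842·√(0.8·0.2 + 0.2·0.8)]² / 0.6² = 9.63, so 10 per arm.

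With the continuity correction: (9.63/4)·[1 + √(1 + 4/(9.63·0.6))]² = 12.75, so 13 per arm. With 10% drop-out: 13/0.9 = 14.4, so 15 per arm. The stated 10 therefore reproduces only without the Yates correction and without drop-out. That is a separate matter, but it means that the starting power is below 80%.

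**Step 2: exact power with perfect classification.** Power is the sum over all pairs (a, b) of Bin(a; n, p₁)·Bin(b; n, p₂) for which the Yates p-value is below 0.05. For 80% against 20% at 10 per arm it is 63.5% (uncorrected chi-square: 80.5%). At 9 per arm, which is 10 × 0.9, the Yates figure is 51.9%.

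**Step 3: misclassification.** The protocol gives no rate, so this is an assumption. With a proportion m misclassified each way in both arms:

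observed rate = p(1 − m) + (1 − p)m

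For m = 0.10: 0.8·0.9 + 0.2·0.1 = 0.74 and 0.2·0.9 + 0.8·0.1 = 0.26.

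| m | Observed rates | Yates power, 10 per arm | Yates power, 9 per arm |
|---|---|---|---|
| 0 | 80% v 20% | 64% | 52% |
| 5% | 77% v 23% | 50.5% | 40% |
| 10% | 74% v 26% | 38% | 29% |
| 15% | 71% v 29% | 27% | 20% |

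**Step 4: one patient.** The result expected under the plan is 8 of 10 against 2 of 10. The Yates statistic is 20·(|8·8 − 2·2| − 10)²/10⁴ = 5.0, above 3.84. Reclassify one patient to give 7 against 2: 20·(|7·8 − 3·2| − 10)²/(10·10·9·11) = 3.23, not significant. The same value follows for 8 against 3. One unguided call can change the result.

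**Step 5: a cut chosen after unblinding.** This was simulated with no treatment effect, a continuous score and the Yates test (100,000 trials):

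| Choice of cut, 10 per arm | Type I error |
|---|---|
| One fixed cut at the median | 1.3% |
| Best of 3 cuts | 3.0% |
| Best of 5 cuts | 4.1% |
| Best of all possible cuts | 8.7% |

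At 9 per arm the last figure is 6.9%. Only the unrestricted search passes 5%.

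**The case against.** **Blinding.** The trial is double-blind (5.2) and the evaluator stays blind to the key (7.4). A reader might infer that type I error is not held at 5% under the plan as written. The protocol does not support that. The figure near 9% needs someone who knows the allocation to search every cut, and if reappearance is recorded blind at each visit there is no such search. What remains is that nothing in the protocol excludes a late cut, and that blinding does not make visit-level decisions consistent.

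**Loss of information.** A reader might also infer that dichotomising throws away most of the score's power. That is not supported either. No standard deviation is given, so any figure rests on an assumed distribution. Entry requires complete response, so patients who do not relapse should score low and the data would look like a mixture, not a shifted normal. At 10 per arm, assumed mixtures with 80% against 20% relapsers give t-test power from 47% (relapsers mean 150, SD 80; others mean 40, SD 40) to 80% (200, SD 30; 20, SD 15), against 64% for Yates. The score may do better or worse. Some of the apparent shortfall of the yes/no test comes from the Yates correction itself (63.5% against 80.5% uncorrected).

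**Other measures and tests.** The GIQLI also has symptom items, so the 0–400 total is not the only symptom record. Section 13 allows a t-test or Mann-Whitney test for quantitative variables, so the total can be compared. Both points stand, but the GIQLI is assigned to quality of life, at first and last visit only, and neither point defines the primary event.

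**Exploratory intent.** Section 13 calls all evaluations exploratory. It also keeps alpha at 0.05 and declares p below 0.05 significant, so this does not remove the need for a definition.

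**Conclusion.** The point holds in a limited form. The primary event has no operational rule on the scale that measures it. Because the event sets the timing of the closing assessments, the gap belongs in the protocol and cannot be closed afterwards.

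The main cost is dilution: from 64% to 38% power at 10 per arm if 10% are misclassified each way, with a range of 50.5% to 27% for 5% to 15%. These rates are assumptions, taken as equal in both arms because of blinding. Inflation of type I error, to about 9% at most, is a possibility the protocol leaves open, not a consequence of following it. No claim is made about how much power the continuous score would add. The change should be made, and the core of the finding does not depend on any of the simulations.

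**What to change.** Before any code is broken:

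1. In sections 8.1 and 8.3, state one rule for reappearance as a rise in the 0–400 total from the patient's own baseline of at least a stated number of points. The investigators choose the number.
2. Apply the same rule at every visit and at early exit, and refer to it where the Summary times the final assessments.
3. In section 13, use that term in place of recidivism and clinical remission.
4. Reconcile the Summary with section 8.1 on whether histological recurrence is part of the primary variable.
5. Name one supportive analysis: the 0–400 total at exit or week 24, compared between arms with adjustment for the baseline total (ANCOVA). State as a limitation that exit scores are taken at different times, some of them because symptoms returned.

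The cost is protocol wording and one more model. The scales are already collected at baseline and every visit. The drawback is that the investigators must commit to a number in advance.

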**8.4. WITHDRAWAL CRITERIA**

Any patient may withdraw from the study at any time without incurring any personal penalty and without the need for explanation. Withdrawal must be noted in the CRF when it occurs, along with the results to date and the reason(s) for withdrawal, if given.

The investigator may also withdraw a patient from the study upon consideration of the risks and benefits thereof, and determination that the former outweigh the latter with continued participation. The CRF must reflect the date and main cause for the withdrawal, as well as any further observations that may be made at the time of withdrawal. Among the reasons for withdrawing a patient early from the study are the following (the main reason should be indicated):

• Lack of efficacy of treatment, e.g.:

– Progression of the illness under study in comparison to baseline.

(in the six weeks following).

– The need to administer a concomitant medication that is prohibited in the treatment of the illness under study.

• Intolerable adverse events.

• Lack of patient cooperation, e.g.:

– Patient request.

– Lack of therapeutic compliance or failure to carry out visits according to the agreed calendar.

– Technical or logistical reasons (e.g., change of patient residence).

– Pregnancy or breast-feeding, either existing or planned.

• Others (must be noted), e.g.:

– Diagnosis different from that of the study.

All patients withdrawing early from the study must be seen within 7 days of the last administration of the medicine used in the study. This final visit is to be duly recorded in the CRF.

The investigator will continue to observe all patients withdrawing early from the study as a result of intolerable adverse events until the findings have been resolved.

**9. ADVERSE EVENTS**

**9.1.** **DEFINITIONS**

9.1.1. Adverse events

Adverse events (AE) are recorded at each visit in the patient notes (source document) and in the CRF.

An AE is any unfavorable medical incident affecting a patient or a clinical trial participant who has been given a pharmaceutical product. It is not necessarily causally related to the treatment. An AE may be, therefore, any sign (including an anomalous laboratory finding), symptom or illness, or accident co-occurring with the use of a medication, whether or not it is related to the medication. Examples include:

. A new diagnosis.

. A symptom requiring medical attention or leading to hospital admission of the patient

(surgery or accident).

. Any assumed adverse reaction to medication.

. Any symptom appearing in the patient’s notes.

. Any event related in time with the administration of the medication of the study and affecting the health of the patient (including changes in laboratory findings).

9.1.2. Serious adverse events

A serious adverse event (SAE) is any unfavorable medical incident that, at any dose:

. Causes death.

. Is potentially fatal.

. Warrants hospital admission of the patient or extension of a pre-existing hospitalization.

. Gives rise to a persistent or significant incapacity.

. Causes a congenital anomaly or birth defect.

Non-serious AEs are all those that do not correspond to any of the categories described immediately above.

9.1.3. Unexpected adverse drug reaction

An unexpected adverse drug reaction (ADR) is one in which the nature or severity of the reaction is not consistent with the available data concerning the product in question.

9.1.3.1. List of expected adverse drug reactions

No adverse events are expected in association with the administration of a gluten-free diet or with the gluten and placebo supplements in the present study.

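### Section 9.1.3.1 expects no adverse events with gluten, yet Section 13 plans on 80% relapsing on it, so the expectedness of the trial's own endpoint event is contradictory

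*Protocol*

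**What the plan says.** **Expected reactions.** The list of expected reactions in Section 9.1.3.1 is one sentence: "No adverse events are expected in association with the administration of a gluten-free diet or with the gluten and placebo supplements" in this trial. It names the gluten supplement, so it cannot be read as covering the diet alone.

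**Planned effect of gluten.** Section 13 takes as its planning assumption that "the rate of recidivism with the reintroduction of gluten would be 80%, and with placebo 20" per cent. It gives the source: "On the basis of results of previous studies it was determined". Section 4.2 makes the demonstration of hypersensitivity to gluten the objective. Section 8.1 fixes the endpoint: "Primary efficacy evaluation variable: Reappearance of clinical digestive signs (24 weeks".

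**What counts as an adverse event.** Section 9.1.1 defines an adverse event broadly, related to treatment or not. Its examples include "Any symptom appearing in the patient’s notes". No exception is made for symptoms that are also the endpoint.

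**What counts as unexpected.** Section 9.1.3 applies the term to a reaction where "the nature or severity of the reaction is not consistent with the available data concerning the product in question".

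**Safety rationale.** The safety criteria in Section 8.1 open with "The gluten-free diet in itself is entirely free of side effects", and Section 10.3 makes a similar statement about the diet. Under Section 7 both groups follow that diet; only the sachet differs.

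**The concern.** Patients enter this trial because they responded completely to removing gluten (Section 6.1). Gluten is then given back to half of them to see whether the illness returns. A protocol that sizes itself on 80% of those patients relapsing cannot also say that nothing untoward is expected from the gluten sachet.

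What is at stake is how the trial's most frequent anticipated event is classified. Two people following the document faithfully could label the same relapse in opposite ways, one by the list in 9.1.3.1 and the other by the definition in 9.1.3. Expectedness also has a use in the text: Section 9.2.2 tells participants to contact the investigator about a serious or unexpected event. Finally, the only statement on the risk of the randomised exposure is that there is none, and the protocol's own planning figures disagree.

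**Working it through.** **Inputs**
- Relapse rates: 80% on gluten, 20% on placebo (Section 13).
- Group size: 10 per arm, 20 in total (Sections 6.3 and 13).
- Drop-out: 10% (Section 13).

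**Step 1. Are these the rates behind the stated size?** The usual two-proportion formula, two-sided 5% and 80% power, without continuity correction:

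n = [1.96·√(2·0.5·0.5) + 0.8416·√(0.8·0.2 + 0.2·0.8)]² / 0.6² = (1.386 + 0.476)² / 0.36 ≈ 9.6, so 10 per arm.

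This matches the stated 10, before drop-out. With the Yates correction that Section 13 names, the result is 13 per arm, and 13/0.9 = 14.4, so 15 after drop-out. That mismatch is a separate matter. The present point needs only the two rates and the group size.

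**Step 2. Endpoint events implied by the plan**

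| | Gluten | Placebo |
|---|---|---|
| 10 per arm | 10 × 0.80 = 8 | 10 × 0.20 = 2 |
| 9 per arm (after 10% drop-out) | 9 × 0.80 = 7.2 | 9 × 0.20 = 1.8 |

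The gluten arm carries 8/(8 + 2) = 80% of the expected relapses. The excess over placebo is 8 − 2 = 6. Treating patients as independent at the planned rates, the binomial probability that at least 5 of 10 gluten patients relapse is 0.994. The probability of more relapses on gluten than on placebo is 0.997. On the protocol's own assumptions, then, relapse on gluten is close to certain to be seen repeatedly.

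**Step 3. Classify one relapse by each section**

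| Section | Question | Answer for a relapse on gluten |
|---|---|---|
| 9.1.1 | Is it an adverse event? | Yes: it is a symptom, and endpoint symptoms are not exempt |
| 9.2.1 | Is it related to the product? | A graded judgement, made without knowing the arm |
| 9.1.3.1 | If related, is it on the expected list? | No: nothing is expected with gluten |
| 9.1.3 | If related, is it inconsistent with available data? | Not in nature: Section 13 cites previous studies for it |

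The last two rows give opposite answers for the same event.

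**Step 4. Does any other text resolve it?** Sections 8.1 and 10.3 vouch for the gluten-free diet. Because both arms follow it, these statements say nothing about the exposure that differs between arms. Section 8.4 lists progression of the illness and intolerable adverse events as separate reasons for withdrawal. It does not say that a relapse falls outside adverse-event recording.

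**The case against.** The best defence is that 9.1.3.1 was meant to cover effects other than the relapse under study. Section 8.4 lends this some support, since it keeps progression of the illness apart from intolerable adverse events. The intention is plausible, but 9.1.3.1 does not state it, and the broad definition in 9.1.1 works against it.

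A second objection is that Section 13 speaks of a relapse rate without defining relapse, and that the Section 1 summary pairs digestive signs with histological recurrence. This stands as a caution: the 80% is not given as a rate for each Appendix 6 symptom. It does not remove the contradiction. Section 8.1 makes return of digestive signs the primary endpoint, and if relapse required both components, every relapse would still include symptoms.

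A third objection is to the reach of the consequences, and here the limits are firm. A reader might infer the following, and the documents do not support it:

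- **That about 10 of 20 patients would be counted as having unexpected reactions.** The sum 8 + 2 = 10 counts relapses. A relapse must first be judged related to the product, under blinding, and the test in 9.1.3 is available data and mentions no list.
- **That safety signals would be buried.** Section 9.2.1 requires nature, severity, seriousness and cause for every event, so events stay distinguishable. The 24-hour report in 9.2.2 is for serious events only, so non-serious relapses would not flood it.
- **That blinding would come under pressure, mainly in the gluten arm.** Section 9.2.2 allows unmasking of isolated cases for participant safety; expectedness does not trigger it.
- **That patients are given wrong risk information.** The information sheet is not among the pages available, so its content cannot be judged.

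**Conclusion.** The statement in 9.1.3.1 is wrong on the protocol's own figures. It sets no expected adverse events with gluten against a planned relapse rate of 80% on gluten (about 8 of 10, against about 2 of 10 on placebo). As a result, a relapse judged related is off the expected list but consistent with available data, and its expectedness is undetermined.

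This rests on three readings: that relapse in Section 13 is the return of digestive signs named in 8.1; that such symptoms are adverse events under 9.1.1, since nothing exempts them; and that the planned rates hold. The contradiction itself does not depend on the exact rate, because any planned excess on gluten conflicts with an empty list.

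The point is worth correcting because the correction is almost free. It concerns safety classification and the stated risk of the challenge. It does not touch the primary comparison.

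**What to change.** - **9.1.3.1:** list return of the digestive symptoms under study (the four in Appendix 6) as expected with gluten.
- **9.1.1 or 9.2.1:** state that these symptoms are recorded as endpoint events, and that the seriousness criteria of 9.1.2 still apply to each of them.
- **9.1.3:** make the definition and the list agree. Since the definition also covers severity, a relapse more severe than the available data suggest would still be unexpected.
- **8.1 and 10.3:** address the gluten challenge itself in terms consistent with Section 13, and not only the diet that both arms share.

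The cost is an amendment of wording and a less reassuring risk statement. Sample size, visits, treatment and analysis stay as they are.
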